### Group P

Dexamethasone: As with adult dosing, trial dexamethasone dosing regimen was amended during the initial stages of the trial to be reduced after the first 2 weeks and to be given pulsed during cycle 1 due to the increase in infection risk (table 2).

**Table 2 T2:** Group P (<18 years) dosing schedule in phase I dose finding

Dose level	**Selumetinib (% of adult MTD**) Cycle 1 D1: single dose Cycle 1 D4–D28: two times dosing Subsequent cycles 2–6: D1–28: two times dosing		**Dexamethasone** Cycle 1 D2–4 and D8-11: 6 mg/m^2^/day, D15–18 and D22-25: 4 mg/m^2^/day Cycle 2 D1–4: 4 mg/m^2^/day Subsequent cycles 3–6, D1–5 only 6 mg/m^2^/day	**Initial design** Applicable prior to DLTs
–1	80%	20 mg/m^2^* two times orally	mg/m^2^*/day orally divided into two doses (as per local practice)	Cohorts 1 and 2
0	100%	25 mg/m^2^* two times orally		Cohorts 3 and 4
+1†	113%–120%‡	28–30 mg‡/m^2^* two times orally		Cohorts 5 and 6

*Body surface area for group P to be calculated according to standard institutional practice.

†Important: The selumetinib dose reverts from the +1 dose level to dose level 0 with the start of cycle 2 as patients will only be exposed to a short pulse of dexamethasone which is not expected to substantially affect selumetinib PK.

‡The proposed increase of dose might be changed based on PK results of dose level 0.

DLTs, dose-limiting toxicities; MTD, maximum tolerated dose; PK, pharmacokinetic.

Selumetinib: Results of two paediatric phase I trials using selumetinib only^22 23^ gave the maximum tolerated dose (MTD) as 2×25 mg/m^2^; thus in the SeluDex trial, 20 mg/m^2^ (80% of the single agent MTD of selumetinib) was chosen as the starting dose for safety reasons (dose level -1), specifically for those patients with CNS disease receiving concomitant intrathecal methotrexate.

### Treatment compliance

Treatment compliance should be discussed with the patient/parent/legal guardian at the beginning of each cycle when study drug is dispensed. The research nurse should complete the relevant sections including recording the morning and afternoon doses and the dates they are to be taken in the diary. All patients/parents/legal guardians will be required to complete a diary with the daily time of administration of the study drugs, which must be returned to the clinic for checking at each visit. If a dose is missed, the reason must be noted in the diary by the patient/parent/legal guardian. Patients/parents/legal guardians should be advised to return any unused investigational medicinal product in the original bottles, in addition to returning any empty bottles. Compliance should be reviewed at the end of each cycle by the site staff via review of the patient diary and discussion with the patient/parent/legal guardian that is to be documented in the medical notes.

### Dose modifications

No dexamethasone dose reductions are permitted during cycle 1 and 2. If identifiable dexamethasone related intolerable toxicity is present during cycle 3 then a dose reduction to 4 mg/m^2^/day is allowed from cycle 4 onwards.

Dose modifications for the following selumetinib-related toxicities are allowed:

Grade 3 neutropenia with infection and/or fever (granulocyte colony-stimulating factor [GCSF] is permitted).Grade 3 or 4 nausea, vomiting, or diarrhoea, if persistent despite optimal antiemetic and/or antidiarrhoeal therapy.Any grade 3 or greater non-haematological toxicity.Any other grade 4 haematological toxicity.

If one or more of these are observed the following action should be taken;

First occurrence: Hold selumetinib until recovery to grade <1 or baseline; restart at original dose level.

Second occurrence: Hold selumetinib until recovery to grade <1 or baseline; keep same dose but reduce to once daily.

Third occurrence: Hold selumetinib until recovery to grade<1 or baseline; use 60% of the original dose but go back to twice daily. For group P: 45 mg reduce to 30 mg; 40 mg to 25 mg; 30–35 mg to 20 mg; 20–25 mg to 10 mg. For group A: 75 mg reduce to 45 mg; 60 mg to 35 mg.

Fourth occurrence: Discontinue selumetinib.

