### Group A

Dexamethasone: Steroids are a backbone of all induction blocks of ALL therapy with dexamethasone, the preferred steroid in the management of patients with ALL (table 1). Initially, dexamethasone was to be administered on a continuous dosing schedule with a weekly total dose of 42 mg/m^2^ for the first course. However, following an observed increase in the risk of infections during the initial stages of the trial, the trial dexamethasone dosing regimen was amended to allow intermittent treatment in blocks rather than continuously, and incorporating a dose reduction from 6 mg/m^2^/day in cycle 1 (d2–4 and D8–11) to 4 mg/m^2^/day during D15–18 and D22–25 of cycle 1. Further dexamethasone is given as a low dose in cycle 2 (D1–4 only: 4 mg/m^2^/day) and then as a high dose again in subsequent cycles (C3–6, D1–5 only: 6 mg/m^2^/day).

**Table 1 T1:** Group A (>18 years) dosing schedule in phase I dose finding

Dose level	**Selumetinib (% of adult MTD**) Cycle 1 D1: single dose Cycle 1 D4–D28: BD dosing Subsequent cycles 2–6: D1-28: two times dosing		**Dexamethasone** Cycle 1 D2–4 and D8-11: 6 mg/m^2^/day, D15–18 and D22–25: 4 mg/m^2^/day Cycle 2 D1–4: 4 mg/m^2^/day Subsequent cycles 3–6, D1–5 only 6 mg/m^2^/day	**Initial design** Applicable prior to DLTs
-1	80%	60 mg two times orally	mg/m^2^*/day orally divided into two doses (as per local practice)	n/a
0	100%	75 mg two times orally		Cohorts 1 and 2
+1†	113%–120%‡	85–90 mg‡ two times orally		Cohorts 3, 4, 5 and 6

*Body surface area for group A to be calculated according to standard institutional practice.

†Important: The selumetinib dose reverts from the +1 dose level to dose level 0 with the start of cycle 2 as patients will only be exposed to a short pulse of dexamethasone which is not expected to substantially affect selumetinib PK.

‡The proposed increase of dose might be changed based on PK results of dose level 0.

DLTs, dose-limiting toxicities; MTD, maximum tolerated dose; n/a, not applicable; PK, pharmacokinetic.

Selumetinib: The dose of 75 mg was chosen as the starting dose for group A (dose Level 0) with the dose only increased if pharmacokinetic (PK) data suggest the addition of dexamethasone decreases selumetinib serum concentrations significantly due to induction of the cytochrome P450 enzyme CYP3A4.^21^

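### The third selumetinib reduction step gives a higher total daily dose than the second for six of the eight listed doses, and two group P milligram entries do not fit the stated 60%

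*Protocol article*

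**What the plan says.** Selumetinib is dosed per administration and given twice a day. Table 1 (group A) lists "75 mg two times orally" at level 0 and "60 mg two times orally" at level -1. Table 2 (group P) gives doses per m², also "two times orally".

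The Dose modifications section then sets four steps, each after a hold and recovery except the last:

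- First occurrence: "restart at original dose level".
- Second occurrence: "keep same dose but reduce to once daily".
- Third occurrence: "use 60% of the original dose but go back to twice daily", followed by a list of reduced doses in milligrams. For adults: "For group A: 75 mg reduce to 45 mg; 60 mg to 35 mg". For group P the list takes 45 mg to 30, 40 to 25, 30 or 35 to 20, and 20 or 25 to 10.
- Fourth occurrence: selumetinib stops.

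The section does not say whether a step is meant to lower the single dose or the daily total, why the third step returns to twice daily, or how 60% is rounded.

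**The concern.** A reader expects successive steps for repeated toxicity to reduce exposure. Here the second step halves the daily total by dropping one of the two administrations, and the third restores that administration at a reduced single dose. If the third-step single dose is more than half the original, the patient restarts on more drug per day than the regimen on which the third toxicity occurred. The triggers are not minor: they include grade 3 neutropenia complicated by infection or fever, and non-haematological toxicity of grade 3 or above. Adverse events are a secondary outcome in both phases, so what patients actually received after repeated toxicity also matters for interpreting them.

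A second, smaller question is whether the listed milligrams agree with the percentage that introduces them.

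**Working it through.** **Inputs.** The original single dose d and the listed third-step single dose n come from the Dose modifications section. Twice-daily dosing comes from Tables 1 and 2.

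**Daily totals.**

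- Original regimen, and after the first occurrence: 2 × d.
- After the second occurrence: 1 × d, so d / 2d = 50% of the original.
- After the third, by the percentage rule: 2 × 0.6d = 1.2d, so 1.2d / 2d = 60% of the original. Applying 60% to the daily total instead gives the same: 0.6 × 2d = 1.2d.
- After the third, by the listed milligrams: 2 × n.

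The percentage rule alone therefore puts the third step at 1.2d / d = 1.20 times the second, a rise of 20% for every dose. This does not depend on rounding.

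**Listed milligrams.** Change = (2n − d) / d. The ratio n/d is also the third-step daily total as a share of the original, since 2n / 2d = n/d.

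| Group | d (mg) | n (mg) | Original (mg/day) | Step 2 (mg/day) | Step 3 (mg/day) | Change, step 2 to 3 | n/d |
|---|---|---|---|---|---|---|---|
| A | 75 | 45 | 150 | 75 | 90 | +20% | 60.0% |
| A | 60 | 35 | 120 | 60 | 70 | +17% | 58.3% |
| P | 45 | 30 | 90 | 45 | 60 | +33% | 66.7% |
| P | 40 | 25 | 80 | 40 | 50 | +25% | 62.5% |
| P | 35 | 20 | 70 | 35 | 40 | +14% | 57.1% |
| P | 30 | 20 | 60 | 30 | 40 | +33% | 66.7% |
| P | 25 | 10 | 50 | 25 | 20 | −20% | 40.0% |
| P | 20 | 10 | 40 | 20 | 20 | 0% | 50.0% |

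The daily total rises for six of eight doses, including both group A doses, is unchanged for one and falls for one. Neighbouring group P doses move in opposite directions: 25 mg falls by 20% and 30 mg rises by 33%.

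**Percentage against milligrams.** Only 75 to 45 mg is exactly 60%. The article states no rounding rule, so rounding to the nearest 5 mg is assumed here:

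| d (mg) | 0.6 × d | Nearest 5 mg | Listed | Agrees |
|---|---|---|---|---|
| 75 | 45 | 45 | 45 | yes |
| 60 | 36 | 35 | 35 | yes |
| 45 | 27 | 25 | 30 | no |
| 40 | 24 | 25 | 25 | yes |
| 35 | 21 | 20 | 20 | yes |
| 30 | 18 | 20 | 20 | yes |
| 25 | 15 | 15 | 10 | no |
| 20 | 12 | 10 | 10 | yes |

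Six of eight agree. The two that do not depart in opposite directions: 45 to 30 mg is above the rule and 25 to 10 mg is below it.

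**The case against.** The best defence is that the article never promises a falling daily total. The return to twice daily is written out explicitly, so it may well be deliberate: the second step cuts frequency and the third cuts the single dose. Every listed single dose does fall at the third step, and every third-step daily total is well below the starting one. Which yardstick is right is a clinical choice. All of this stands, and it limits the point to asking for the intent and for consistency. It does not remove the comparison with the second step, which is the regimen on which the third toxicity occurred. Nor does the article give a reason that would explain a rise at 30 mg and a fall at 25 mg.

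Three stronger readings are tempting and are not supported:

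- A reader might infer that the milligram list as a whole contradicts the 60%. It does not: six entries agree under ordinary rounding, which capsules swallowed whole would require. Capsule strengths are not given and might account for the other two.
- A reader might infer that sites are left unable to act. They are not: the list gives a definite dose for every starting dose it names, and a site can follow it.
- A reader might infer that the list is incomplete, since it has no adult entry for the 85–90 mg level and no group P entry below 20 mg or above 45 mg. A journal article may leave such detail to the full protocol. For the adult +1 level, moreover, "The selumetinib dose reverts from the +1 dose level to dose level 0 with the start of cycle 2", so an entry would be needed only for a third occurrence within cycle 1.

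**Conclusion.** The inconsistency between the second and third steps is real and follows from the article's own text. The daily total goes from 50% to 60% of the original under the stated rule. With the listed milligrams it rises for six of eight doses, by 14% to 33%. Two group P entries, at 67% and 40%, are unexplained by the 60% rule, subject to the assumed 5 mg rounding and the unknown capsule strengths. The calculation takes occurrences as counted in sequence for one patient, and the original dose as the single dose first assigned.

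A reader might infer that the third step exceeds the starting dose, or that it undermines the trial's main results. Neither holds. Third-step totals are 40% to 67% of the original. The step reaches only patients with a third qualifying toxicity after two holds, in groups of at most 21. The dose-limiting toxicity window is cycle 1, response is assessed at day 28, and patients without at least a partial response at that point stop treatment. The primary endpoints are therefore hardly affected. The point should be corrected because it bears on patient safety and on the exposure behind the adverse-event data, but it is not a flaw in the statistical design.

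**What to change.** The sponsor's clinical team should reconcile the second-occurrence step, the third-occurrence step, the 60% rule and the group P entries for 45 mg and 25 mg. The revised text should state whether each step is meant to lower the single dose or the total daily dose. If a higher daily total at the third step is intended, it should say so and give the reason. It should also state the rounding convention, so that percentage and milligrams can be checked against each other. Which figure or step order is right is for the sponsor to decide; none is proposed here.

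The cost is a protocol amendment to wording and list. The sample size, the dose-finding model and the phase II decision rule are unaffected.

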### Concomitant medication

Patients should avoid consuming large amounts of grapefruits, seville oranges and any other products that may contain these fruits, for example, grapefruit juice. In addition, patients should not take any vitamin E supplements. Restricted medications are listed in table 3.

**Table 3 T3:** Restricted medications within the SeluDex trial

Acetazolamide Aminoglutethimide Antacids Anticholinesterases Anti-hypertensives Aprepitant Barbiturates Beta-naphthoflavone Carbamazepine Carbenoxolone Clarithromycin Coumarin anticoagulants Diltiazem Diuretics Efavirenz Ephedrine Erythromycin	Fluconazole Fluvoxamine Glucocorticoids Hypoglycaemic agents, for example, insulin Indinavir Itraconazole Ketoconazole Loop diuretics Methylcholanthrene Modafinil Nafcillin Nefazodone Nelfinavir Nevirapine Norethindrone Non-steroidal anti-inflammatory drugs (NSAIDs) Omeprazole	Oral contraceptives Oxcarbazepine Phenobarbital Phenytoin Pioglitazone Prednisolone Primidone Rifabutin Rifampicin Ritonavir Salicylates Saquinavir Suboxone Telithromycin Thiazide diuretics Troglitazone Verapamil St John’s Wort

### Trial outcomes

#### Phase I

The primary objective for the phase I dose-finding component is to determine the recommended phase II dose (RP2D) of selumetinib in combination with dexamethasone, as defined by the occurrence/non-occurrence of dose limiting toxicities (DLTs) in the trial-defined assessment period. The trial will achieve this through the use of the continual reassessment method (CRM).^24^ DLTs will be assessed from the first dose on cycle 1, day 1 up until cycle 1, day 28 during phase I only. A DLT is defined as any toxicity which is dose limiting, is not attributable to the disease or disease-related processes under investigation, and is considered at least possibly related to selumetinib or dexamethasone (see the Dose limiting toxicities section).

Secondary outcomes for the phase I component are:

The occurrence of adverse events (AEs) as measured by Common Terminology Criteria for Adverse Events (CTCAE) V.4^25^ and causality assessment.PK variables of selumetinib in combination with dexamethasone from the concentration time profile (area under the plasma concentration-time curve (AUC), C_max_, T_max_, t_1/2_).Response to treatment assessed by complete remission (CR) rate at 28 days as measured by morphological and minimal residual disease (MRD) response in BM and for patients with CNS involvement only clearance of cerebrospinal fluid (CSF) blasts at 28 days.Difference in PK of selumetinib (ΔAUC) when selumetinib is administered as single agent and in combination with dexamethasone.

#### Phase II

The primary objective for the phase II expansion component will be to assess preliminary antileukaemic activity of the selumetinib/dexamethasone drug combination as defined by morphological response (CR, CR with incomplete platelet recovery (CRi), PR, non-response and for patients with CNS involvement only, clearance of CSF blasts) 28 days post-treatment end. Response evaluation will be undertaken with BM response at day 28, including MRD and CSF surveillance for CNS positive patients with standard cytology. A patient will be classified as having a response if they achieve CR or CRi at the day 28 assessment (with an acceptable window of day 15–35).

Secondary outcomes for the phase II component are;

The occurrence of AEs as measured by CTCAE V.4 and causality assessment.The occurrence/non-occurrence of DLTs in the trial defined assessment period.PK variables of selumetinib in combination with dexamethasone from the concentration time profile (AUC, C_max_, T_max_, t_1/2_).Difference in PK of selumetinib (ΔAUC) when selumetinib is administered as single agent and in combination with dexamethasone.MRD response in BM at 28 days.

Exploratory outcomes of the trial for both phases of the trial include exploratory pharmacodynamic (PD) biomarker studies if clinical responses are observed. These will include levels of phosphorylated ERK by flow cytometry in leukaemic cells from patients at several time points (cycle 1 day 1, cycle 1 day 4 and end of treatment visit), as well as retrospective mRNA profiling, including the apoptotic initiator Bcl-2-like protein 11 (Bcl2-L-11/BIM).^20 26^

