### Dose limiting toxicities

DLTs will be assessed from the first dose in cycle 1 day 1 up until cycle 1 day 28 during phase I. A haematological DLT is defined as BM aplasia/hypoplasia, defined as overall marrow cellularity less than 25% (malignant infiltration or other causes are excluded), which does not recover by cycle 1 day 28. This includes an absolute neutrophil count of less than 0.5×10^9^/L and a non-transfusion dependent platelet count of less than 25×10^9^/L due to BM aplasia/hypoplasia. In addition, grade 4 febrile neutropenia, and any grade 5 AE are also defined as a haematological DLT.

Non-haematological DLTs in group A are defined as left ventricular ejection fraction <45% as measured by echocardiogram; and in group P as >15% reduction in shortening fraction from baseline by echocardiogram. Results must be viewed by a consultant cardiologist to confirm that there has been a genuine deterioration in cardiac function. In addition, any grade 5 AE, grade 3 nausea or vomiting on or before C1D28 only which does not resolve to <grade 2 within 48 hours (with or without supportive care), grade 3 mucositis on or before C1D28 only which does not resolve to grade <2 within 48 hours (with or without supportive care), any other grade 3 or 4 non-haematological toxicity, specifically excluding: alopecia; dexamethasone related CTCAE grade 3 toxicities (eg, hyperglycaemia, muscle weakness, psychosis, avascular necrosis); tumour lysis syndrome; and increased alanine transaminase or aspartate aminotransferase.

Suspected DLTs will be reviewed and confirmed by the Trial Safety Committee (TSC) during dose decision meetings at the end of each cohort during phase I.

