#### Phase II

The phase II part of the trial will include patients from the phase I component that were dosed at the RP2D plus patients recruited into the expansion cohort. The number of phase I patients taken forward to the phase II assessment will be at least 4 in each group and the maximum number of patients to be recruited in the expansion cohort will be 9 in each group, giving a total of 13.

Based on data published by the TACL group (CR rate of 44% for second relapses and 27% for third relapses^28^) and seeing as we expect a mixture of second, third and higher relapses in paediatric patients and similar if not worse relapse rates for adult patients, we estimate the overall response rate on standard treatment to be approximately 35%.

This phase will use a Bayesian approach to investigate the true response rate in each group. A beta-binomial conjugate analysis will be used to create a posterior probability distribution of the true response rate using the observed trial data combined with a beta (1, 1) minimally informative prior. The trial design is based on the decision criteria that if there is a high probability (>0.80) that the true response rate is >35% then this will indicate that the treatment is worthy of further research. With 13 patients, this design works reasonably well with a low probability of 0.08 of incorrectly concluding that the treatment is worthy when the true response rate is only 25% and a high probability of 0.82 of correctly concluding that the treatment is worthy when the true response rate is 55%.

If the response rates are similar in both groups, then information may be borrowed across Groups A and P to provide more accuracy in determining the true response rate for both groups collectively

There are no planned subgroup or interim analyses.

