### AEs reporting and analysis

The collection and reporting of AEs as measured by CTCAE V.4 will be in accordance with the Research Governance Framework for Health and Social Care and the requirements of the National Research Ethics Service. Definitions of different types of AEs are listed in online supplemental appendix 5; this includes abnormal laboratory findings which are considered clinically significant. The reporting period for AEs will be from the date of commencement of protocol defined treatment until 28 days after the administration of the last treatment. The investigator should assess the seriousness and causality (relatedness) of all AEs experienced by the patient (this should be documented in the source data) with reference to the protocol. In addition, DLTs will be assessed for the phase I part of the trial only. All will be reported using the applicable electronic case report form (CRF).

10.1136/bmjopen-2021-059872.supp5Supplementary data

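### DLT occurrence is listed as a phase II secondary outcome, but DLT assessment is confined to phase I, so the outcome is missing for the 1 to 9 expansion patients per group

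*Protocol article*

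**What the plan says.** In the protocol article, under Trial outcomes, Phase II, the secondary outcomes include "The occurrence/non-occurrence of DLTs in the trial defined assessment period". No assessment period is defined there for phase II.

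Three other places define when DLTs are assessed:

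- Trial outcomes, Phase I: "DLTs will be assessed from the first dose on cycle 1, day 1 up until cycle 1, day 28 during phase I only".
- Dose limiting toxicities: "DLTs will be assessed from the first dose in cycle 1 day 1 up until cycle 1 day 28 during phase I". The word 'only' is absent here, but suspected DLTs are to be confirmed by the Trial Safety Committee (TSC) during "dose decision meetings at the end of each cohort during phase I".
- AEs reporting and analysis: "DLTs will be assessed for the phase I part of the trial only".

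Under Statistical analysis plan, Phase II, the phase II set consists of "patients from the phase I component that were dosed at the RP2D plus patients recruited into the expansion cohort". The same section adds: "The number of phase I patients taken forward to the phase II assessment will be at least 4 in each group". At most 9 expansion patients per group bring the total to 13. Adverse events, with CTCAE grade and causality, are collected in both phases.

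**The concern.** The only DLT assessment period that the article defines belongs to phase I, and so does the only confirmation step. An expansion patient therefore has no assessment, no period and no route to confirmation, yet belongs to the set on which a DLT outcome is to be reported. An analysis plan cannot summarise determinations that the protocol says are not made.

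What is at stake is how well the toxicity of the chosen dose is described by the end of the trial. The expansion may supply most of the patients treated at that dose. The Discussion reports three fatal suspected reactions, each followed by an urgent safety measure, the last in September 2019, while the first patient was recruited in May 2018. Some early DLT data may therefore come from a superseded dexamethasone schedule. Expansion patients would add DLT data under the current one.

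**Working it through.** **Inputs (protocol article, Statistical analysis plan and Study design).** Phase I maximum 12 per group; phase II total 13 per group; at least 4 carried forward; at most 9 in the expansion; recruitment 13 to 21 per group and 26 to 42 overall; target DLT rate 17%; Beta(1,1) prior; success if P(response rate > 0.35) > 0.80.

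**1. The plan's own figures.** With n = 13 and a Beta(1,1) prior, 5 responders give P(rate > 0.35) = 0.641 and 6 give 0.816, so the rule needs at least 6. The exact binomial P(X ≥ 6) is 0.0802 at a true rate of 25% and 0.8212 at 55%. The stated 0.08 and 0.82 reproduce. This rule uses response only, so the DLT question does not touch it.

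**2. Recruitment and the uncovered patients.** Let k be the number of phase I patients per group carried forward at the RP2D. Recruitment per group is 12 + (13 − k).

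| k | expansion, 13 − k | recruited per group | share of the 13 without DLT assessment |
|---|---|---|---|
| 4 | 9 | 21 | 9/13 = 69% |
| 12 | 1 | 13 | 1/13 = 8% |

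Doubling 13 and 21 gives the stated 26 to 42. So k runs from 4 to 12, and 1 to 9 patients per group have no DLT determination.

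**3. Precision of the directly observed DLT rate at the RP2D.** With no DLT in n patients, the one-sided 95% upper bound is 1 − 0.05^(1/n):

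- n = 4: 0.527
- n = 8: 0.312
- n = 12: 0.221
- n = 13: 0.206

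With 1 DLT in 13, the bound solves (1 − p)^13 + 13p(1 − p)^12 = 0.05. At p = 0.316 the left side is 0.684^12 × (0.684 + 13 × 0.316) ≈ 0.0105 × 4.792 ≈ 0.050, so the bound is about 32%. The two-sided exact 95% intervals with one DLT are 0.6% to 80.6% for 1/4 and 0.2% to 36.0% for 1/13.

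**4. How likely the zero-event case is.** At the 17% target, P(no DLT) is 0.83^4 = 0.475 with 4 patients and 0.83^13 = 0.089 with 13. The 21% bound is therefore a favourable case, seen about 9% of the time at the target rate.

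**The case against.** The strongest reply is that little safety information is lost. Expansion patients have their adverse events graded and attributed until 28 days after the last treatment, any death is recorded, and the TSC meets at least every 6 months in phase II. Most of this stands: what is missing is the formal DLT determination, not the safety data. Grade and causality alone do not complete the definition, however. It also needs marrow cellularity and its recovery by day 28, cardiologist review of a cardiac change, resolution within 48 hours for some events, named exclusions and TSC confirmation. Whether the relevant tests are scheduled for expansion patients is in a supplementary appendix that is not shown.

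The phase II item might also be meant only for the carried-forward patients. The text does not say so, and the phase II evaluable population is everyone who received any treatment.

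Three stronger readings are tempting, and the documents do not support them:

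- A reader might infer that the outcome is never collected. The 4 to 12 carried-forward patients per group fall under the phase I assessment.
- A reader might infer that the DLT rate at the RP2D rests on about 4 patients. Four is the stated minimum. The continual reassessment method (CRM) also uses up to 12 phase I patients per group across dose levels. Only a raw proportion, in the worst case, rests on 4.
- A reader might set the 53% and 21% bounds against 27% and say that 13 patients exclude an unacceptable rate while 4 do not. The 27% figure belongs to a phase I stopping rule for the lowest dose: stop if the probability of a rate above it exceeds 0.85. It is not a limit on the RP2D, and a single DLT in 13 already puts the bound at about 32%.

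**Conclusion.** The contradiction is real and nothing in the article resolves it. Followed literally, a listed phase II safety outcome cannot be determined for 1 to 9 of the 13 patients per group. The consequence is confined to that outcome and to the precision of the DLT rate at the RP2D. In the worst case 4 patients per group have direct DLT data instead of 13; when 12 are carried forward the loss is one patient and is negligible (zero-event bound 22% against 21%).

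The count of 4 to 12 assumes that every carried-forward patient is DLT-evaluable. Under the phase I evaluability rule, some who stop early for reasons unrelated to treatment would not be, and the article allows no replacement. The bounds treat patients as independent with a common DLT rate and ignore the CRM's borrowing across doses.

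**What to change.** Reconcile the phase I and phase II outcome lists, the Dose limiting toxicities section and the AEs reporting and analysis section.

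**Preferred.** State that DLTs are assessed over cycle 1 days 1 to 28 in expansion patients as well, with the existing definition unchanged. Name the TSC's phase II meetings as the point of confirmation. Define the DLT-evaluable denominator for phase II, because the present evaluability rule covers phase I only and the phase II population is anyone treated. Keep CRM dose decisions in phase I. Report the DLT rate with its interval for all patients treated at the RP2D in each group, and do not use the 27% stopping threshold as a limit on it.

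**Alternative.** If DLT assessment is meant for phase I only, limit the phase II item to the carried-forward phase I patients, or delete it.

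**Cost.** The preferred change adds DLT review and confirmation for at most 9 patients per group, and any test that the definition needs and the schedule does not already give them. It changes no sample size, dose rule or response criterion. The alternative costs one edited line but gives up the added precision.
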